## 7 METHODOLOGY

### 7.1 Study design, dialyzers and dialysis conditions

This study is a prospective multicenter randomized comparative cross-over trial.

Four different dialysis facilities (AURA Paris, Yvetot clinic, AIDER clinic and Toulouse university hospital center) will be involved in the study.

Eligible patients will be assigned to receive either post-dilution HDF (first two centers) or conventional high-flux HD (last two centers) for 4 weeks. During this period, all patients will be sequentially dialyzed with 4 different dialyzers (one/week, the two first sessions of the week; the

last session of the week being performed with the patient's own dialyzer and used as a wash out session): Leoced 21HX, Polypure 22S+, Rexsys 27H and VIE-21A.

The sequence of dialyzers use will be randomly assigned: per center, device × week allocation scheme will be generated by random permutation of a block of 4 (computer generation). All patients in a given center will follow the scheme allocated to this center. The randomization sequence will be centralized and computed by the statistician.

No run-in period before entering in the active study phase will be performed

Dialysis sessions will be conducted according to usual procedures of the center, with increased monitoring and control of the patients treated with the tested hemodialyzers.

Patients will be treated in HD or post-dilution HDF, according to the usual conditions, specific to each patient. The frequency of dialysis (3 sessions per week), the duration of dialysis (3- 4h), the blood flow of the extracorporeal blood circuit ( $\geq 300$  mL/min), the type (dialysate bicarbonate or other) and the dialysate flow (700 mL/min) will remain unchanged or will be documented in case of modification.

In case of need for adjustment, or changes in prescription of the medication, these changes will be documented. The modifications will respect recommendations.

[figure not shown]

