### 7.4 Samples

Blood samples needed for the study will be drawn weekly (for a total of 4 weeks) during the midweek session from the arterial line of the extracorporeal circuit without additional puncture before and after dialysis.

Each withdrawal will include:

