## 9 STATISTICAL ANALYSIS

### 9.1 Calculation of the sample size

This study has mainly a pragmatic exploratory orientation. It aims to try to detect differences in performance between dialyzers tested whose importance is clinically relevant. To do this, it was considered that, for the measured variables, a Cohen effect size of about 0.6 in two-to-two comparisons would meet this criterion of relevance. Under these conditions, in a bilateral situation and setting a 5% alpha risk and a 20% beta risk, a minimum of 32 patients is required.

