#### General remark

The design of this study involves the comparison of 4 dialyzers for a same patient over 4 weeks. Each week begins with the use of one studied dialyzer over 2 sessions, the second session serving as a reference. Then, the third session of the week is performed with the usual dialyzer. On this basis, the participating nephrologists have considered that any risk of persistent effect (carry-over) could be excluded and that the duration of the study was short enough to rule out a period effect related to a change in the subject's clinical status (no effect period). In addition, a randomization of the Latin square type was not considered possible for practical organization reasons at each center level.

As a result, a random order of dialyzer use was decided once (random switching of 4 elements) and this order will be applied for all patients of a same center: all patients in a given center will follow the scheme allocated to this center.

The sequence of dialyzers use will be randomly assigned: per center, device  $\times$  week allocation scheme will be generated by random permutation of a block of 4 (computer generation).

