### 9.2 Principle of the analyzes

The included population will be described in terms of demographic and medical inclusion data.

Two populations of analysis are planned: the global population including all the patients with at least one dialyzer tested and the per-protocol population (PP) including all the subjects having tested the 4 dialyzers.

The main analyzes will be conducted on the PP population and additional sensitivity analyzes on the overall population.

The main analyzes will use a univariate generalized linear model integrating the variable tested as a dependent variable and the standard hemodialysis factor (2 levels: conventional HD or HDF), the dialyzer factor (4 levels) and the center factor (4 levels) as fixed factors. A full factorial model will be applied. Two-to-two comparisons will then be conducted by adjusting the alpha risk according to the Bonferonni method.

All analyses will be carried out with Statistical Package for Social Sciences version 18.0 (IBM Inc, USA).

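### The main model in section 9.2 has no patient term, although every patient is measured on all four dialyzers, so the standard errors of the dialyzer contrasts are too large

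*Protocol*

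**What the plan says.** Section 7.1 gives the design: "This study is a prospective multicenter randomized comparative cross-over trial". The general remark in section 9.1 adds: "The design of this study involves the comparison of 4 dialyzers for a same patient over 4 weeks". Section 7.4 fixes the measurement schedule: "Blood samples needed for the study will be drawn weekly (for a total of 4 weeks) during the midweek session". A patient who completes the study therefore supplies four values of the primary outcome, the beta-2 microglobulin reduction ratio (section 4.1), one per dialyzer.

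Section 9.2 then states the model: "The main analyzes will use a univariate generalized linear model integrating the variable tested as a dependent variable", with "the standard hemodialysis factor (2 levels: conventional HD or HDF), the dialyzer factor (4 levels) and the center factor (4 levels) as fixed factors". It continues: "A full factorial model will be applied". Pairwise comparisons with a Bonferroni adjustment follow. The main analysis set is "the per-protocol population (PP) including all the subjects having tested the 4 dialyzers", so every patient in it contributes four rows. On sample size, section 9.1 concludes that "a minimum of 32 patients is required", for a Cohen effect of about 0.6 in pairwise comparisons, two-sided 5% alpha and 20% beta.

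**The concern.** A cross-over is chosen so that each patient serves as his or her own control and differences between patients drop out of the dialyzer comparison. The listed factors do not achieve this. Center removes differences between centers, but not between patients within a center. The full factorial adds only interactions among modality, dialyzer and center. Differences between patients therefore stay in the residual against which dialyzers are tested, and four correlated values per patient are treated as independent.

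The error runs in two directions. Dialyzer contrasts, including those on the primary outcome, are tested against too large an error, so real differences can be missed. HD versus HDF is a comparison between patients, and it is tested as if there were four times as many independent units as there are.

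**Working it through.** **Inputs.** From the protocol: 32 patients, 4 dialyzers, 4 centers, effect 0.6, two-sided 5%, 80% power, Bonferroni adjustment. Derived: 32 x 4 = 128 rows if all complete; 4 x 3/2 = 6 pairs, so alpha = 0.05/6 = 0.0083. Assumed: 8 patients per center; total within-center variance 1; rho = 0.3, 0.5 or 0.7; no week effect.

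**The plan's own figure of 32.**
- Paired, two-sided 5%, 80% power: n = ((1.960 + 0.842)/0.6)^2 = 21.8, so 22 patients (24 with the t distribution).
- Unpaired: 2 x 21.8 = 43.6, so 44 per dialyzer (45 with t).
- Neither gives 32. Paired calculations with a Bonferroni divisor that section 9.1 does not mention come close: alpha/3 gives 30 (normal) or 32 (t), and alpha/6 gives 34 or 38.
- At n = 32, a paired effect of 0.6 has 91% power at 5%. Thirty-two unpaired values per dialyzer have 67%.

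**Standard error of a dialyzer difference.** Modality is determined by center, so the model reduces to center-by-dialyzer cells, with 128 - 16 = 112 residual df. Its residual variance is 1, so the model's SE is sqrt(2/32) = 0.250. The patient component cancels in a within-patient difference, so the true SE is sqrt(2(1-rho)/32). The ratio is 1/sqrt(1-rho).

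| rho | SE as modelled | True SE | Overstated by |
|---|---|---|---|
| 0.3 | 0.250 | 0.209 | 1.20 |
| 0.5 | 0.250 | 0.177 | 1.41 |
| 0.7 | 0.250 | 0.137 | 1.83 |

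**Power for a difference of 0.6 across-patient SD at alpha 0.05/6.**
- As written, normal approximation: Phi((0.6/0.250 - 2.638)/sqrt(1-rho)) = 39%, 37% and 33%. Simulation of 4 centers x 8 patients x 4 dialyzers, with the t reference on 112 df, gives about 37%, 36% and 32%; repeat runs agree to within about one point.
- With a patient term: residual df = 128 - 32 - 3 - 9 = 84, and noncentrality = 0.6/true SE = 2.87, 3.39 and 4.38 against a critical t of 2.70. Power is 57%, 75% and 95%.
- If 0.6 is instead a paired effect, power with a patient term does not depend on rho: about 71% for a paired t test on 31 df, or about 75% with the pooled 84 df error (the same as the rho = 0.5 case, since 0.6/sqrt(2 x 0.5) = 0.6).

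**Type I error of a dialyzer contrast.** At rho = 0.5 and nominal 5%, simulation gives about 0.7% without a patient term and 4.9% with one.

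**HD versus HDF.** The mean of four correlated values has variance (1 + 3 rho)/4, while the model assumes 1/4. The SE is understated by sqrt(1 + 3 rho) = 1.38, 1.58 and 1.76. The false-positive rate at nominal 5% is 2(1 - Phi(1.96/sqrt(1 + 3 rho))) = 15.5%, 21.5% and 26.6%, before any true difference between centers is added.

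**The case against.** The strongest defence has five parts.

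1. **The dialyzer error is conservative.** This stands: with positive rho, false dialyzer claims are not inflated, and in the balanced per-protocol set the estimated dialyzer differences are unchanged. A reader might infer that the plan would produce spurious dialyzer differences or biased estimates; it would not. What is lost is power, and the intervals are too wide. The study's exploratory orientation does not excuse this, because section 9.1 still sets alpha, power and a relevant effect.

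2. **The size is not fixed by the protocol.** This also stands. It states neither rho nor the SD behind Cohen's 0.6. At rho = 0 the two models agree, and at rho = 0.3 the inflation is moderate.

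3. **A later plan could add the patient term.** This is weak. Section 9.2 lists the terms of the main model, so a plan that added a patient term would depart from it.

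4. **A full repair might seem to need a week effect.** The design does not support requiring one. Within a center, all patients follow one dialyzer order, so week and dialyzer are confounded there and separable only through differences between centers. With week and dialyzer-by-modality both fitted, about 26% of randomly drawn sets of four orders leave at least one dialyzer contrast non-estimable. In the others the median SE is about 1.18 times larger, and median power falls to about 40%, 57% and 84% at rho 0.3, 0.5 and 0.7. The general remark also argues that no period effect is expected.

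5. **A patient term might seem to rescue HD versus HDF.** It does not. Modality is assigned by center, two centers each. With center fixed, the contrast compares only these four centers; with center random, it has about 2 df.

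**Conclusion.** The model written in section 9.2 does not match the cross-over design and gives wrong standard errors whenever rho is not zero. With positive rho, dialyzer contrasts carry standard errors too large by 1/sqrt(1-rho), and HD versus HDF carries one too small by sqrt(1 + 3 rho). Both directions follow from the design; the sizes rest on the assumed rho of 0.3 to 0.7. The power comparison further assumes the across-patient SD, no week effect and 32 completers.

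A reader might conclude that 32 patients are too few. The documents do not show that: 32 does not follow from the stated inputs, but it exceeds the 22 to 24 needed for a paired effect of 0.6 at unadjusted 5%. What falls short of 80% under the stated assumptions is the planned analysis, at about 32% to 37% after Bonferroni.

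**What to change.** In section 9.2, replace the univariate model by a linear mixed model, or an equivalent repeated-measures model, with a random intercept for patient and fixed effects for dialyzer, center nested in modality, and dialyzer-by-modality. Take the Bonferroni pairwise dialyzer contrasts from it for the beta-2 microglobulin reduction ratio and the secondary variables. With dialyzer-by-modality in place of center-by-dialyzer, the within-patient df are 128 - 32 - 3 - 3 = 90 rather than 84, which hardly changes the figures above.

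Do not require week in the main model. Consider it only as a sensitivity analysis, after checking that the sequences actually drawn make the dialyzer contrasts estimable. State that HD versus HDF is reported descriptively because modality is assigned by center.

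The cost is one paragraph of text. No new data, visits or patients are needed. The trade-off is that HD versus HDF would no longer be presented as a formal test.

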## 1 PROJECT SUMMARY

Objectives of this prospective multicenter randomized cross-over study are to evaluate the influence of two dialysis treatments (HD vs post-dilution HDF) with four high-flux (polysulfone or polyethersulfone) dialyzers i) in the clearance evaluation for small, middle and large molecular weight substances and ii) in the modification of several biological responses including parameters of inflammation and nutrition. In addition, a comparative quantification of perdialytic albumin losses using either a partial collection of continuous spent dialysate or the total dialysate collection will be performed in a subgroup of patients. Primary outcome will be  $\beta$ 2-microglobulin removal. Secondary outcomes will be i) extraction of other uremic solutes ii) parameters of inflammation and nutrition and iii) comparative quantification of perdialytic albumin losses.

32 chronic kidney disease patients treated with extrarenal replacement therapy and issued from 4 dialysis centers will be assigned to receive either post-dilution HDF (2 first centers) or conventional high-flux HD (2 other centers) for 4 weeks. During this period, all patients will be sequentially dialyzed with 4 different dialyzers (one/week): Leoced 21HX, Polypure 22S+, Rexasys 27H and VIE-21A. The sequence of dialyzers use will be randomly assigned. All patients in a given center will follow the scheme allocated to this center.

Dialysis conditions will remain unchanged for each patient: 3 sessions/week, 3-4 hours/session, blood flow (QB) of 300-400mL/min, ultrapure bicarbonate buffered dialysate, dialysate flow (QD) in the range 500-700mL/min.

Blood samples will be drawn weekly during the midweek dialysis session before and after dialysis. Routine laboratory analyses including serum urea, creatinine and PO4 (all being evaluated pre- and post-dialysis) will be locally performed. Specific biomarkers including serum  $\beta$ 2-microglobulin, myoglobin, free light chain  $\kappa$ , Beta Trace Protein, myostatin, orosomucoid, CRP, TNF- $\alpha$ , IL-6, albumin and transthyretin will be performed on frozen samples in a central laboratory.

Results of this study should bring additional information on the performance and biocompatibility of the 4 hemodialyzers tested and help in personalizing device prescription according to dialysis treatment (HD or HDF) and patient profile.

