## 5 PATIENTS

#### 5.1 Inclusion criteria

- ❑ Adult patient with chronic kidney disease dialyzed for at least one month and treated with the modality used in the center (HD or HDF) for the study
- ❑ Regarding post-dilution HDF mode, patient treated with a minimum convective volume of 20L (cf EuDIAL guidelines)
- ❑ Patient treated with high permeability membrane, with high surface area dialyzer  $\geq 1,8 \text{ m}^2$
- ❑ Patient with vascular access allowing a blood flow rate with a minimum of 300 mL/min
- ❑ Patient covered by the social French health organism
- ❑ Patient informed of the study goals and having signed the informed consent

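### Each center delivers one modality, so the full factorial model in 9.2 cannot separate HD vs HDF, or its interaction with dialyzer, from center differences

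*Protocol*

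**What the plan says.** - **Objective.** Protocol section 1 opens with the aim "to evaluate the influence of two dialysis treatments (HD vs post-dilution HDF) with four high-flux" dialyzers, and closes by saying that the results should help match the device to the modality. Section 4 also says that extraction will be assessed by technique.
- **Allocation of modality.** Section 1: patients "will be assigned to receive either post-dilution HDF (2 first centers) or conventional high-flux HD (2 other centers) for 4 weeks". Section 7.1 repeats this: "assigned to receive either post-dilution HDF (first two centers) or conventional high-flux HD (last two centers) for 4 weeks". Section 5.1 requires patients to be already "treated with the modality used in the center (HD or HDF) for the study". No center uses both modalities.
- **Main model.** Section 9.2 takes the modality factor ("2 levels: conventional HD or HDF), the dialyzer factor (4 levels) and the center factor (4 levels) as fixed factors") and then states: "A full factorial model will be applied". It mentions neither nesting nor a random effect. Bonferroni-adjusted pairwise comparisons follow.
- **Sizing.** Section 9.1 calls the study mainly exploratory and bases the sample size of 32 on pairwise dialyzer comparisons, not on HD vs HDF.

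**The concern.** A full factorial model presumes that every level of one factor can occur with every level of the others. Here, knowing the center tells you the modality. The two factors compete for the same information, and center takes all of it. The same holds for modality by dialyzer once center by dialyzer is in the model.

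At stake are two results that sections 1 and 4 lead the reader to expect: the HD vs HDF comparison, and whether the ranking of dialyzers differs between HD and HDF. Software will usually not stop on such a model. It drops redundant columns and may still print HD and HDF means by averaging center cells. A reader would take the gap between those means as a modality effect, when it also contains every other difference between the two pairs of centers.

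**Working it through.** **Inputs.** Four centers, two per modality (sections 1 and 7.1); four dialyzers per patient (7.1); 32 patients (9.1); three fixed factors and all their interactions (9.2). Eight patients per center is an assumption. The ranks do not depend on it. The residual df depends only on the total of 32 × 4 = 128 sessions.

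**Step 1: cells.** Crossing the factors gives 2 × 4 × 4 = 32 cells. Each center has one modality, so only 4 × 4 = 16 can hold data.

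**Step 2: columns and rank.** Full indicator coding gives

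1 (intercept) + 2 (modality) + 4 (center) + 4 (dialyzer) + 8 (modality × dialyzer) + 8 (modality × center) + 16 (center × dialyzer) + 32 (three-way) = 75 columns.

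The computed rank is 16. Center, dialyzer and center × dialyzer alone, with no modality term, also give rank 16. The modality terms add nothing.

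**Step 3: df of each term, as the gain in rank after the other terms named.**

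| Term | After | df |
|---|---|---|
| Modality | center | 4 − 4 = 0 |
| Modality × dialyzer | center × dialyzer | 0 |
| Modality × center, and three-way | all others | 0 |
| Center | modality | 2 |
| Center × dialyzer | modality × dialyzer | 6 |

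Modality is not estimable even in a model with main effects only. The reason is algebraic: the HDF indicator equals the sum of the two HDF center indicators. The contrast that can be estimated is the mean of the two HDF centers minus the mean of the two HD centers, and this equals the modality effect plus the average center difference.

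**Step 4: what survives.** All 16 possible center by dialyzer cell means are estimable. A dialyzer pair within HDF is the average of the two HDF centers' differences; likewise within HD, and over all four centers. These contrasts are unaffected by the nesting.

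**Step 5: the nested partition.** With center nested in modality, the 127 df after the intercept split as

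1 (modality) + 2 (center within modality) + 3 (dialyzer) + 3 (modality × dialyzer) + 6 (center within modality × dialyzer) + 112 (residual).

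The 112 pools 28 df between patients (32 − 4) with 84 within patients (28 × 3). If centers count as a source of variation, modality is judged against 2 df and modality × dialyzer against 6 df. The two-sided 5% critical t is 4.30 on 2 df, against 1.98 on the 112 residual df.

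**Step 6: can week be added?** Section 9.1 applies one dialyzer order to all patients of a center, so week and dialyzer coincide within a center. Over all combinations of four independently drawn orders (first order fixed by symmetry, 24³ = 13,824), a fixed part with center, dialyzer, modality × dialyzer and week is rank-deficient in 3,600, or 26%.

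**The case against.** The best defense is that the comparison the trial is sized for is not harmed. The primary outcome in section 4.1 is the β2-microglobulin reduction ratio with no modality contrast, section 9.1 concerns differences between dialyzers, and the study is described as exploratory. This stands, and it limits the point to HD vs HDF and the difference in dialyzer effects between modalities. It does not remove the point, because sections 1 and 4 do present modality as something to be evaluated and 9.2 puts it in the main model.

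Three stronger readings are tempting, and the documents do not support them.

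- *The study cannot inform device choice by modality.* A reader might infer this from the 0 df. But that use needs dialyzer contrasts within HD and within HDF, and these are estimable (step 4). Only the difference between the two sets is confounded with center.
- *The protocol passes modality off as randomised.* Sections 7.1 and 9.1 apply randomisation only to the dialyzer order, and 5.1 says that patients are already on their center's modality. No text claims otherwise.
- *Nesting alone inflates the type I error to 15–27%.* Testing modality against the 112-df residual gives about that range with no center effect, at assumed within-patient correlations of 0.3–0.7. That inflation comes from leaving out the patient: the variance of a patient mean is understated by the factor 1 + 3ρ, and it would arise without nesting too. Only the further rise to about 29–37% reflects centers, at an assumed center ICC of 0.05. The protocol gives neither quantity, so these figures illustrate the risk and do not measure it.

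Dropping center × dialyzer would return 3 df to modality × dialyzer, but 9.2 specifies the full factorial, and the contrast would still be confounded with center.

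**Conclusion.** The point holds in a limited form. The main model in 9.2 contradicts the allocation in sections 1, 5.1 and 7.1: modality and modality × dialyzer each have 0 df beyond the center terms, 16 of 32 cells are empty, and 75 columns have rank 16. The model gives no HD vs HDF effect, and no difference in dialyzer effects between modalities, that is separable from center. This follows from the allocation alone and needs no assumption about variances, correlations or patients per center.

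Dialyzer comparisons, overall and within each modality, are not affected. Treating centers as a source of variation leaves 2 df for modality and 6 df for modality × dialyzer, so any inference about modality would be weak even under a correctly written model.

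**What to change.** - **Section 9.2, model.** Delete the full factorial statement. State that center is nested within modality and patient within center, so that dialyzer comparisons are made within patient. Name these comparisons, overall and within each modality, as the main contrasts.
- **Sections 1, 4 and 9.2, modality.** Label HD vs HDF, and the difference in dialyzer effects between modalities, as descriptive and confounded with center. Give intervals that reflect two centers against two: modality against the 2 between-center df, and modality × dialyzer against center within modality × dialyzer on 6 df. Keep that last term in the model; without it the interaction would be judged against within-patient error, which ignores centers. A center variance based on 2 df is very poorly estimated, which is a further reason to report modality descriptively.
- **Week.** Do not add it as a fixed effect before checking estimability for the four orders actually drawn.

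The cost is wording only; no procedure, visit or sample changes. The downside is that the HD vs HDF statement becomes descriptive, which is all that this design supports.

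### Section 9.1 claims 80% power at 5% alpha, but section 9.2 tests the pairs by single-step Bonferroni; Holm or Shaffer's step-down on the same pairs recovers part of the shortfall

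*Protocol*

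**What the plan says.** Protocol section 9.1 gives the aim as follows: "It aims to try to detect differences in performance between dialyzers tested whose importance is clinically relevant". It takes "a Cohen effect size of about 0.6 in two-to-two comparisons" as the relevant difference and sets the error rates "in a bilateral situation and setting a 5% alpha risk and a 20% beta risk". From these it concludes that "a minimum of 32 patients is required". It does not say whether the effect size is paired or unpaired, and it mentions no adjustment for several comparisons.

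The General remark after 9.1 describes a within-patient design: "The design of this study involves the comparison of 4 dialyzers for a same patient over 4 weeks". Four dialyzers make six pairs.

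Section 9.2 specifies a full factorial model with modality, dialyzer and center as fixed factors, and then runs the pairwise comparisons by "adjusting the alpha risk according to the Bonferonni method". The number of comparisons is not given.

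**The concern.** The sample size section and the analysis section describe tests at different levels. Section 9.1 claims 80% power with an alpha of 5%, while 9.2 tests each pair at 5% divided by the number of pairs. Unless 32 contains an allowance that the text does not mention, the power of the planned comparisons is lower than stated.

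Part of that loss is also avoidable. Single-step Bonferroni holds every pair to the strictest threshold, even after other pairs have been rejected. Step-down tests relax the threshold as rejections accumulate and keep the same familywise error. At stake is the chance of detecting a 0.6 difference in the β2-microglobulin reduction ratio between two dialyzers, with no change in the number of patients.

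**Working it through.** **Inputs.** From 9.1: d = 0.6, two-sided 5%, 80% power, n = 32. From the General remark: four dialyzers, so 4 × 3 / 2 = 6 pairs. Assumptions: d is on the scale of the paired difference, the data are normal with equal variances and correlations, and all 32 patients are in the per-protocol set.

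**The protocol's own figure.**
- Paired, normal approximation: ((1.960 + 0.842) / 0.6)² = 21.8, so 22 patients. With the t distribution: 24.
- Unpaired: 2 × 21.8 = 43.6, so 44 per group.

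Neither is 32. The figure does arise from a paired t-test at 0.05/3 with 80% power, at 5% with 90% power, or from 24 / (1 − 0.25) = 32. The normal approximation at 0.05/6 gives 33.6, so 34. The protocol states none of these routes.

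**Power per pair at n = 32.** The noncentrality is 0.6 × √32 = 3.394.

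| Test | Level | Critical t | Power |
|---|---|---|---|
| Separate paired t, 31 df | 0.05 | 2.040 | 90.8% |
| Separate paired t, 31 df | 0.05/6 = 0.0083 | 2.818 | 71.4% |
| Pooled within-patient error, 31 × 3 = 93 df | 0.05/6 | 2.696 | 75.6% |

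The paired t-test needs 38 patients for 80% power at 0.05/6.

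**Step-down alternatives on the six pairs.** Holm compares the ordered p-values with 0.05/6, 0.05/5, 0.05/4, 0.05/3, 0.05/2 and 0.05. Shaffer uses the logic of four means: the number of pairwise nulls that can be true together is 6, 3, 2, 1 or 0. Once one pair is rejected, at most three nulls can remain true. Its thresholds are therefore 0.05/6, then 0.05/3 for the next three ordered p-values, then 0.05/2 and 0.05. No threshold in either procedure is stricter than 0.05/6, so any pair that Bonferroni rejects is rejected by both.

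Simulated power per 0.6 pair (40,000 to 200,000 trials per pattern), Bonferroni / Holm / Shaffer:

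| True means | Pooled error | Separate paired t |
|---|---|---|
| One dialyzer differs from three | 75.4 / 78.3 / 81.3% | 71.8 / 75.0 / 78.7% |
| Two versus two | 75.5 / 80.4 / 82.1% | 71.4 / 77.0 / 79.2% |
| 0, 0.3, 0.3, 0.6 | 75.6 / 76.1 / 76.9% | 71.3 / 72.2 / 73.4% |

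If all adjacent dialyzers are 0.6 apart, separate tests give 71.4 / 89.8 / 89.8%. With no true difference, the familywise error is about 4% for all three procedures. The chance of finding at least one true difference is practically unchanged, because the first threshold is 0.05/6 in each.

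**The case against.** **Bonferroni is valid and the trial calls itself mainly exploratory.** This stands. Nothing in 9.2 inflates the error rate; the point is one of efficiency and of consistency with 9.1.

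**The number of pairs may be fixed in a statistical analysis plan.** This also stands. A reader might infer that the significance threshold can be picked after the data are seen, because the full factorial model also allows 12 within-modality pairs or 28 pairs of modality-by-dialyzer cells. The protocol does not support that: its aim points to six dialyzer pairs, and the count is commonly left to a later plan. Nor should the power at 0.05/12 or 0.05/28 be computed with 32 patients (62% and 50%). Within-modality pairs rest on about 16 patients if the split is even, which gives 21.7% and 13.7%. Much of that fall comes from the smaller n. Of the 28 cell pairs, 4 × 4 = 16 compare different patients, so paired power does not apply to them.

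**The shortfall depends on the scale of d.** If 0.6 refers to the between-patient SD, the paired effect is 0.6 / √(2(1 − ρ)), with ρ the correlation between weeks. At 0.05/6 and 80% power, the paired t-test needs 51 patients for ρ = 0.3, 38 for ρ = 0.5, 31 for ρ = 0.6 and 24 for ρ = 0.7. With ρ of about 0.6 or more, 32 patients suffice even under Bonferroni. The protocol gives neither the scale nor ρ.

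**Section 9.2 lists no patient term.** If the analysis really has none (ρ = 0, 112 residual df), power with one dialyzer differing is 39.1% (Bonferroni), 41.4% (Holm) and 44.9% (Shaffer). Step-down testing still helps, but it does not come near 80%.

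**Conclusion.** The point holds as an efficiency improvement and a mismatch between two sections. For six pairs, d = 0.6 on the paired scale and 32 evaluable patients, single-step Bonferroni gives 71% (separate tests) or just under 76% (pooled error) per pair, against the stated 80%. In the first three patterns, step-down testing adds about 0.5 to 7 points with pooled error and about 1 to 8 with separate tests. The gain is larger when several dialyzers truly differ, and absent for the first rejection.

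A reader might infer that step-down testing restores the planned power in full. It does not: with means 0, 0.3, 0.3, 0.6, Shaffer reaches only 76.9% with pooled error, and with separate tests it stays below 80% in all three patterns of the table. A variant that first requires a significant overall dialyzer test and then starts at 0.05/3 does somewhat better (78–83% with pooled error in the same patterns). It is not uniformly better than Bonferroni, because the overall test blocked a Bonferroni rejection in up to about 1% of simulated trials. Only Holm and Shaffer without that gate never reject less.

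The familywise guarantee covers only the family to which the procedure is applied. Six-pair testing run separately in each modality gives about 7.9% over the 12 pairs.

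**What to change.** - **Section 9.2:** for the primary outcome, replace single-step Bonferroni by Holm's or Shaffer's step-down test (0.05/6, then 0.05/3 for the next three ordered p-values, 0.05/2, 0.05, if the family is six pairs). Name the family; the six dialyzer pairs are the natural reading of 9.1.
- **Section 9.1:** restate the power for 32 patients at the adjusted alpha, and say on which scale the effect size of 0.6 is defined.
- **Both sections:** the gain presupposes a within-patient analysis, so 9.2 should make the patient term explicit.

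Whether within-modality comparisons are confirmatory or exploratory is for the sponsor to decide. Sections 1 and 4 want performance judged by technique, so leaving those comparisons outside the family has a price.

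The cost is a few sentences and no extra patients. The adjusted p-values have to be computed outside the SPSS menu, and Bonferroni-width confidence intervals may not always agree with the step-down decisions.
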